### Sample Size Estimation

This is a phase 1 safety and feasibility trial. There are no data available for reference because no clinical study of RIC and exercise therapy in patients with confirmed acute ischemic stroke (mRS ≤ 2, NIHSS score 6–16) has yet been completed. Hertzog (27) has suggested that 10–20 patients in each group are sufficient to assess the feasibility of a pilot study, while Dobkin (28) has shown that 15 patients in each group are usually enough to decide whether a larger multicenter trial should be conducted. A similar number of samples was selected in two other related protocols (29) (Lv et al., Frontiers in Neurology in press ). We therefore set our recruitment goal to 20 patients per group in the present study. The results of this study will be used to determine the safety and feasibility of RICE and be used to estimate the sample size and perform power calculations necessary to plan the phase 2 trials.

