### Statistical Analysis

All statistical analyses will be performed using the statistical software SAS (version 9.1.3; SAS Institute, Cary, NC). Outcome event analyses will be based on the intention-to-treat (ITT) principle, including all randomly enrolled subjects. Subjects' baseline categorical variables will be recorded in percentages (%), and continuous variables will be recorded as means and standard deviations or medians and interquartile ranges. The comparison of baseline parameters of the study subjects will be performed with the Pearson chi-square test and either the *t*-test or the Wilcoxon rank sum test for the categorical and continuous variables, respectively.

The distribution difference of the 90-day mRS scores between the two groups will be evaluated using the common ratio. The public odds ratio of the mRS scores on the 90th day will be evaluated by the sequential logistic regression model. The ratios between the mRS categories (0–2 and 3–6) and adverse events will be estimated with the improved Poisson regression. Infarct volume and β coefficient of the NIHSS score will be estimated by multiple linear regressions. Efficacy assessment will be adjusted based on age, gender, NIHSS baseline score, baseline condition, stroke subtype, intravenous alteplase treatment, and mechanical thrombectomy. The homogeneous dominance ratio of each subgroup will be analyzed *via* the Breslow–Day test to analyze the functional independence of the subgroup for 90 days. The significance level will be set at 0.05 for all tests.

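### Adjusting for seven factors in 40 patients inflates type I error in the two day-90 mRS models, and the subgroup tests have very little power

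*Protocol article*

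**What the plan says.** The Sample Size Estimation section of the protocol article sets the size from pilot-study rules of thumb: "We therefore set our recruitment goal to 20 patients per group in the present study". It gives no effect size or power.

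The Statistical Analysis section names three kinds of model:
- Ordinal mRS: "The public odds ratio of the mRS scores on the 90th day will be evaluated by the sequential logistic regression model". I read this as a common odds ratio from a proportional-odds model.
- Binary mRS: "The ratios between the mRS categories (0–2 and 3–6) and adverse events will be estimated with the improved Poisson regression". I read this as modified Poisson regression with a robust variance.
- Continuous outcomes: "Infarct volume and β coefficient of the NIHSS score will be estimated by multiple linear regressions".

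It then states: "Efficacy assessment will be adjusted based on age, gender, NIHSS baseline score, baseline condition, stroke subtype, intravenous alteplase treatment, and mechanical thrombectomy". For subgroups, "The homogeneous dominance ratio of each subgroup will be analyzed" with a Breslow–Day "test to analyze the functional independence of the subgroup for 90 days", which I read as a test that the odds ratios are homogeneous. One significance level, 0.05, applies to every test. The section gives no reduced model or fallback and does not label these tests exploratory. The categories of subtype, the content of the baseline-condition term and the subgroups are not defined.

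**The concern.** The covariate list is a positive choice, not an omitted detail, and it is long for 40 patients. The robust variance in modified Poisson and the likelihood-ratio test in the ordinal model are both large-sample tools. With about one or two favourable outcomes per slope, the robust standard error tends to be too small and the nominal 5% level need not hold. Rare categories can also leave a covariate cell with no favourable outcome, so that its coefficient runs off to infinity.

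At stake is the use made of the results. The Sample Size Estimation section says they will inform the sample size and power of phase 2, and the Perspective section lists efficacy as an aim. An unstable effect with too narrow an interval is a poor input to that.

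**Working it through.** **Inputs from the article.** 40 patients, 1:1; seven factors; 0.05 for all tests (two-sided assumed). The Discussion cites good-prognosis rates of 46% for NIHSS 7–10 and 23% for 11–15.

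**Assumptions.** The article gives no prevalences or subtype classification. The simulations took age and NIHSS as the only prognostic factors (log-odds 0.5 and 0.8 per SD), alteplase 15–30%, thrombectomy 5–15%, and subtype with two levels or with five (shares 35, 20, 30, 5 and 10%). There is no figure in the plan to reproduce, because no operating characteristic is stated.

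**Slopes.** Treatment 1 + age 1 + gender 1 + NIHSS 1 + condition 1 + subtype 1 to 4 + alteplase 1 + thrombectomy 1 = 8 to 11, plus intercepts.

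**Events per slope.** 0.23 × 40 = 9.2 and 0.46 × 40 = 18.4 favourable outcomes. The extremes are 9.2/11 = 0.8 and 18.4/8 = 2.3 per slope.

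**Modified Poisson, no treatment effect, uncorrected robust Wald test, 1,500 simulated trials per scenario.** Rejections at nominal 5%, whether counted over clean fits only or over all fits:

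| Favourable rate | 8 slopes | 11 slopes |
|---|---|---|
| 30% | 8.1–10.9% | 8.9–14.5% |
| 50% | 6.4–7.6% | 8.2–9.2% |
| 70% | 6.8% | 7.9% |

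With treatment, age and NIHSS only, the figure is 4.0–5.6% (30% and 50% rates). The Monte Carlo standard error at 5% is √(0.05 × 0.95/1,500) = 0.6 points. It is larger where few fits are clean: for 14.5%, based on 0.221 × 1,500 ≈ 331 fits, it is √(0.145 × 0.855/331) = 1.9 points.

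In a separate 4,000-trial null simulation (five-level subtype, 25% alteplase, 12% thrombectomy), among fits without a diverging coefficient, the mean standard error of the treatment effect was 0.48 against a true SD of 0.62, a ratio of 0.77. With age and NIHSS only the SD was 0.47.

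**Diverging coefficients.** If a category holds 5% of patients, that is 0.05 × 40 = 2 patients. At a 30% favourable rate, neither has a favourable outcome with probability 0.7² = 0.49, and the log-link coefficient for that category then diverges. In simulation (clean fit = full rank, converged, no coefficient above 10), 8 slopes gave no clean fit in 1–21% of trials, or 39–60% with thrombectomy 5% and alteplase 15%. With 11 slopes it was 29–78%, or 67–88%. The treatment coefficient itself exceeded 3 in only about 1% of runs or fewer.

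**Ordinal model, likelihood-ratio test.** In 1,000 trials: 7.8% (8 slopes) and 10.1% (11 slopes), against 5.4% and 5.6% with age and NIHSS only. A 400-trial run gave 9.3% and 12.9%, but its unadjusted test also ran high (7.0% and 8.0%), so the larger run is the better guide. Fits failed in 0.3–0.4% (8 slopes) and 7–9% (11 slopes).

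**Linear models.** Type I error was 3.9–6.2%, so no inflation. Residual degrees of freedom are 40 − 9 = 31 or 40 − 12 = 28, against 40 − 4 = 36 with two covariates. With five subtype levels about 14% of trials were rank-deficient. That is essentially the chance that a 5% or a 10% level is empty: 0.95⁴⁰ + 0.90⁴⁰ = 0.129 + 0.015 = 0.144.

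**Breslow–Day.** Two equal subgroups give 10 patients per arm in each. Even at 46% favourable, the expected count is 10 × 0.46 = 4.6, below 5. In 5,000 simulated trials per scenario the test rejected in 5.8–6.1% under homogeneity, was computable in at least 97.7%, and had 10–19% power for a fourfold ratio of odds ratios. Several such tests accumulate error: seven independent ones (illustrative; the number is not stated) give 1 − 0.95⁷ = 0.302.

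**The case against.** Adjusting for prognostic baseline factors is good practice, and the list is clinically sensible. The affected outcomes are secondary; the primary outcome is safety, and the adjustment sentence is confined to efficacy. An analysis plan, if one exists, could handle sparse categories, variance corrections and fallbacks. All of this stands and limits the severity. It does not remove the point, because the article itself fixes the seven factors, and following it as written gives the error rates above.

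The size also rests on inputs the article does not supply. The 46% and 23% come from a cited source whose definition of good prognosis is not shown, and NIHSS scores of 6 or less are described as more favourable still. At higher event rates or with a two-level subtype the inflation is modest, as low as 6.4%.

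A reader might infer more than this supports:
- That every efficacy analysis misses its 5% level. The linear models do not.
- That the Breslow–Day tests double the error. Each holds about 6%; their weakness is sparse cells and power.
- That the models cannot be fitted. Divergence is frequent in modified Poisson under some codings, but almost always in a nuisance term, and the treatment effect stays estimable. The ordinal model seldom fails.
- That phase 2 would be launched on a false positive. The article sets no go/no-go rule on an efficacy p-value.

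**Conclusion.** The point holds for the two mRS models. With the seven-factor list in 40 patients, type I error is about 6–11% (8 slopes) or 8–14% (11 slopes) for modified Poisson, and about 8–13% for the ordinal model, instead of 5%. In modified Poisson the robust standard error also understates the true variability of the treatment effect.

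These figures assume a robust Wald test for the Poisson model, a likelihood-ratio test for the ordinal model, and the covariate prevalences listed. The loss of precision further assumes that the five factors beyond age and NIHSS carry little prognostic information of their own. The linear models lose only degrees of freedom. The subgroup tests are nearly uninformative rather than misleading one by one.

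This should be fixed, but it is not critical, because the outcomes are secondary in a pilot.

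**What to change.** For the ordinal and modified Poisson models of day-90 mRS, prespecify adjustment for age and baseline NIHSS only, both continuous. Add a small-sample variance correction to the Poisson model. In simulation the short model held 4.0–5.6% even without that correction, so it is a safeguard. Report subgroup results as counts and estimates, or label them exploratory, instead of testing each at 0.05.

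The change costs wording only, with no extra patients, visits or data. It should be made before unblinding, since shortening the model after a failed fit would be data-driven. The downside is that a chance imbalance in alteplase, thrombectomy or subtype would appear in the baseline table and not be modelled.

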## Discussion

Exercise rehabilitation has been confirmed to be one of the most effective approaches to improving prognosis and preventing lasting complications after stroke (30). It is an indispensable component in the organizational management of cerebrovascular diseases (31). The latest domestic and international guidelines for stroke rehabilitation recommend early rehabilitation for patients with acute stroke (11). However, the optimal model of early rehabilitation is still controversial. Recent studies have confirmed that very early exercise rehabilitation exacerbates brain injury (12). The promotion of very early exercise rehabilitation is also limited in actual clinical practice for many reasons, such as unstable vital signs, low cardiorespiratory fitness, and poor muscle strength and muscle power in stroke patients (15).

Ischemic conditioning is an approach that provides neuroprotection (32) and has been observed to be efficacious in promoting rehabilitation for patients with global cerebral ischemia (33). The use of ischemic conditioning has been clinically demonstrated through hypobaric and normobaric hypoxia (34, 35). RIC has also been used widely in other contexts (36), including reduction of myocardial injury after ischemia in large animal models and human trials (37). In studies of cerebral pathologies, RIC has improved cognition in patients with subcortical ischemic vascular dementia (38) and conferred neuroprotective effects after acute ischemic stroke (39). It offered neuroprotection through enhanced cerebral perfusion, cerebral collateral formation, and tolerance of cerebral ischemia (40, 41). Furthermore, studies have shown that long-term RIC training can reduce nerve injury (42), promote nerve remodeling and angiogenesis (25), and promote the motor function of paralyzed limbs (43, 44). Chronic and repetitive RIC has been applied to clinical trials and is expected to exert its protective role against cerebral ischemia and repeated stroke in a long-term fashion (40). It has also been demonstrated to improve performance in sports medicine, akin to the physiological improvement that is appreciated in routine exercise training (24). Some underlying mechanisms of RIC and exercise have been evidenced to overlap—both therapies demonstrate increased expression of heat shock proteins, enhanced involvement of the nitric oxide (NO) pathway, modification of ATP-sensitive potassium (K_ATP_) channels' functionality, enhanced antioxidant capacity, induction of autophagy, involvement of the opioid system, and regulation of the immune and inflammatory system (24). Together, these processes enhance neurogenesis, angiogenesis, and defense against oxidative stress in the brain after an ischemic event.

RIC and exercise have similar temporal windows in which they induce benefits in the rehabilitative stage of stroke recovery. They also have similar effects and mechanisms in performance improvement. These overlapping biochemical and clinical characteristics appoint RIC as a suitable candidate to fill the “gap” that is seen in very early rehabilitation, of which physical exercise is currently the sole therapy. Using RIC for the very early time frame would avoid the deleterious impact of exercise while potentially reaping RIC's unique benefits including ischemia and hypoxia tolerance. In other words, the combination of novel early RIC training followed by exercise rehabilitation, which is known to be effective, could form a new type of early stroke rehabilitation model. The model would enable the mechanisms of exercise therapy known to be beneficial to stroke patients, such as increased neurogenesis and angiogenesis in the brain, to be initiated earlier than is normally feasible. The subsequent application of traditional exercise therapy would reinforce these processes and lead to greater clinical progress and better prognosis after several months. This novel rehabilitation strategy will be applied for the investigation of functional recovery promotion, disability reduction, and prognosis improvement in patients with ischemic stroke.

The NIHSS score has been demonstrated to be a good prognostic indicator of stroke outcome (45). NIHSS scores of ≤6 indicate a high likelihood of good prognosis; scores of 7–10 and 11–15 indicate good prognosis rates of 46 and 23%, respectively (45); and scores of ≥16 suggests a poor prognosis and a high possibility of death or severe disability (46). Patients with disabilities after stroke mostly have NIHSS scores >6, which was set as the lower bound for our inclusion criteria in this study. Moreover, it has been reported by previous studies that it is difficult for patients with severe stroke-induced disability (NIHSS score ≥16) to perform early exercise rehabilitation due to various reasons, such as severe symptoms, unstable conditions, and intolerance of early out-of-bed rehabilitation treatment (15). Therefore, patients with NIHSS scores >16 will be excluded from this study. To summarize, moderate acute ischemic stroke patients with NIHSS scores of 6–16 will be included in this study, as these patients will likely be able to participate in the given tasks for rehabilitation and subsequently have a favorable prognosis.

RIC is a non-invasive, feasible, and promising rehabilitative method for patients recovering from ischemic stroke. It has been demonstrated that post-stroke RIC training can be carried out safely within 6–24 h of acute ischemic stroke attack and induce a significant neuroprotective and neurorehabilitative effect (39). Hence, RIC training will be initiated within 24 h after stroke onset in this study.

Very early exercise rehabilitation with physical exercise after stroke may aggravate brain injury and reduce the rate of good prognosis at 3 months post-cerebrovascular event (47). Previous expert consensus also recommends that exercise rehabilitation treatment be conducted within 48–72 h after stroke, after which patients have regained stable vital signs and no longer have acutely deteriorating neurological symptoms (12). Therefore, in this study, out-of-bed exercise rehabilitation will be carried out 72 h after stroke attack, that is, on the fourth day of stroke. Early RIC combined with follow-up exercise training is a novel early rehabilitation model for acute stroke patients; therefore, we set the duration of RIC and exercise rehabilitation to be 14 days according to the protocol of “A Very Early Rehabilitation Trial” (AVERT) (48), the most well-known and evidence-based clinical study on early rehabilitation of stroke.

In this way, our study will employ two treatments that are known to be effective in stroke rehabilitation at their respective temporal windows that are known to maximize benefits and reduce adverse events. This temporal optimization will enable stroke patients to benefit from the individual advantage of RIC and exercise rehabilitation and perhaps from a temporal and synergistic role of the two therapies.

There are some limitations to this study. First, as previous research is lacking, the sample size was calculated based on previous relevant literature (27, 28). Additionally, the patient population is highly targeted in this study: we have limited the inclusion criteria to patients with moderate acute cerebral infarction and moderate-to-high disability rate (NIHSS scores 6–16). Therefore, the results may not be accurately generalizable to all patients with acute cerebral infarction. Future directions should seek to apply this modem of post-stroke therapy to patients with infarcts varying in size and severity as well as diverse degrees of post-stroke disability as determined by the NIHSS score.

## Perspective and Prospective

The aim of this study is to clarify the safety and efficacy of early RIC combined with follow-up exercise training as rehabilitation for patients with moderate acute cerebral infarction. The experimental results will reflect a new strategy for stroke rehabilitation that can improve the clinical prognosis of patients with acute cerebral infarction.

## Ethics Statement

The studies involving human participants were reviewed and approved by Medical Ethical Committee of Beijing Luhe Hospital, Capital Medical University. The patients/participants provided their written informed consent to participate in this study.
